#### Control Group

The control group will be asked to continue with its regular exercise routine, and the group will be asked to not make any changes during the study. Interested participants in the control group will be offered the opportunity to attend ongoing yoga classes as frequently as they would like, following study completion.

#### Assessment Protocol

As per the CONSORT extension for pilot RCTs, the number of participants screened for eligibility, randomly assigned, received intended treatment, and assessed for each objective will be recorded [81]. Study data will be collected in the Physiotherapy department at Dalhousie University and managed using Research Electronic Data Capture (REDCap) software (REDCap Inc) [87]. The authors will provide access to the study’s REDCap (REDCap Inc) data upon request. Table 2 outlines the outcome variables and measurement tools.

**Table 2 table2:** Outcomes and measurement tools.

Outcome	Measurement tool	Objective measure or self-report
Yoga readiness (previous experience with yoga, injuries and ability level)	Yoga readiness questionnaire (yoga group only)	Self-report
Cognitive performance	Communicating Cognitive Concerns questionnaire; Brief Cognitive Ability Measure	Self-report; objective
Motor function (balance, walking speed)	Community Mobility and Balance Scale; 10-meter walk test	Objective; objective
Mental health	Hospital Anxiety and Depression Scale	Self-report
Quality of life	Medical Outcomes Survey	Self-report
Medication adherence	Simplified Medication Adherence Questionnaire	Self-report
Physical activity	Rapid Assessment of Physical Activity; Fitbit Flex 2—total distance walked (km) and steps taken per day	Self-report; objective
Participant satisfaction, safety, comfort, fatigue, and benefits	Postparticipation survey (yoga group only)	Self-report

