### Ethical Considerations

The study protocol was approved by the REB (protocol reference #1022158). The procedures will be followed in accordance with institutional ethical standards and the Helsinki Declaration. The trial was registered on ClinicalTrials.gov. Proposed amendments to the protocol will be submitted for review to the REB. For ethical reasons, we cannot ask participants to avoid making medication changes; any changes participants make to their medications will be documented. Unanticipated or adverse events will be reported immediately to the REB. Participant confidentiality and autonomy will be maintained throughout the study, and data will be anonymized and secured. Study data will be stored in a locked office at Dalhousie University. Electronic data will be stored in encrypted form and will exclusively be accessed by the research team. Restricting access to data on-site until the data have been appropriately coded and deidentified will mitigate the risk of residual disclosure. All data will be destroyed after 7 years. Decisions to stop participating will be respected. To offset participants’ personal and travel costs, we will provide bus tickets for assessments and yoga sessions, and we will provide parking reimbursement, snacks, and honoraria for the assessments.

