##### Primary Measures

Many domains of feasibility will be assessed by both participants and study personnel using monitoring processes and a 13-item paper-based post-intervention questionnaire, which includes both questions on a Likert scale ranging from strongly disagree to strongly agree and open-ended questions (see Multimedia Appendix 1):

Project coordination (team building, communication and meetings, collaboration, consensus building, troubleshooting, scheduling, protocol consistency, and timelines). Any issues with (or changes to) the study protocol or scheduling will be documented.Participant issues (recruitment, comfort, satisfaction, safety, attendance, time commitment, attrition, and reasons for ineligibility drop out/declining to participate), as assessed by the postintervention questionnaire and documentation by the study coordinator.Assessment protocol elements (time and personnel requirements, usefulness of outcome variables, participant burden, and feasibility) will be recorded by the study coordinator.Intervention protocols (time, equipment, and personnel requirements) will be recorded by the study coordinator.Data quality (completeness, intra/interparticipant variability, interpretability, and trends) will be checked by the study coordinator. Per the CONSORT checklist, our a priori adherence and satisfaction criteria will be met if participants attend 70% of the yoga sessions and if 70% of the participants are satisfied with the yoga intervention as per the postparticipation questionnaire.

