### Participant Safety

Participants will be monitored throughout the yoga sessions and the assessments. If a participant presents with any medical or safety concerns, the supervising physiotherapist will provide the appropriate first aid or injury treatment; then, the supervising physiotherapist will refer the participant to the participant’s family physician for follow-up. Any harms or unanticipated effects will be recorded as per the CONSORT checklist [81]. Owing to the low-risk nature of the study, we do not anticipate any additional safety or medical issues associated with the yoga interventions.

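### Safety, comfort and fatigue are solicited from the yoga arm only, and only that arm is watched at sessions, so harms are ascertained unequally and controls' own view of the trial is not collected

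*Protocol article*

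**What the plan says.** Table 2 (Assessment Protocol) has one row for "Participant satisfaction, safety, comfort, fatigue, and benefits". Its tool is a "Postparticipation survey (yoga group only"), and it is classed as self-report.

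On observation, Participant Safety states: "Participants will be monitored throughout the yoga sessions and the assessments". Both arms attend assessments; only the yoga arm attends sessions.

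Other sources are not limited to one arm:

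- Participant Safety: "Any harms or unanticipated effects will be recorded as per the CONSORT checklist".
- Ethical Considerations: "Unanticipated or adverse events will be reported immediately to the REB".
- Primary Measures, on participant issues, a list that includes safety, time commitment and attrition: "as assessed by the postintervention questionnaire and documentation by the study coordinator".
- Primary Measures, on the assessment protocol: "participant burden, and feasibility) will be recorded by the study coordinator".

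The first objective is the feasibility of the study protocol and procedures, as groundwork for a full-scale trial. Primary Measures says that both participants and study staff will assess feasibility.

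**The concern.** Falls, injuries, new pain and tiredness can occur over 12 weeks whether or not someone practises yoga. If one arm is seen three times a week by a physiotherapist and then asked about safety and fatigue, while the other is seen once and not asked, background events are more likely to be noted in the first arm. Harms listed by arm could then look like an effect of yoga when part of the difference comes from how hard anyone looked.

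The second matter is the primary aim. A full-scale trial would also have a control arm, whose members must accept their allocation, leave their exercise routine unchanged and attend assessments estimated at 2 hours. Under Table 2 they are not asked how they found any of this. Their experience reaches the feasibility assessment only through staff records.

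**Working it through.** The plan gives no figure to reproduce. The check is a count of contacts, a comparison of sources by arm, and a look at what 25 participants could support.

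**1. Monitored contacts after randomisation.** Randomisation follows the baseline assessment (Randomization), so that visit cannot capture events on allocated treatment.

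- Yoga, maximum: 3 × 12 = 36 sessions (Attendance Policy), plus the 12-week assessment: 36 + 1 = 37.
- Yoga at 70% attendance: 0.70 × 36 + 1 = 26.2, about 26.
- Control: 1.

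Accelerometer data are downloaded after weeks 1 and 12. If the week 1 download is in person, which the article does not say, each arm gains one contact: 38 against 2 at most.

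**2. Sources of information by arm.**

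| Source | Yoga | Control |
|---|---|---|
| Survey on safety, comfort, fatigue | yes | no |
| Monitoring at sessions | up to 36 | none |
| Monitoring at the 12-week assessment | 1 | 1 |
| Recording of harms; reports to the ethics board | yes | yes |
| Coordinator records (burden, time commitment, attrition, drop-out reasons) | yes | yes |
| Own rating of trial procedures | only through the survey, as far as its items cover them | no |

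The arms differ in solicited report and in observation. They do not differ in the duty to record.

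**3. Effect on a tabulation.** Suppose both arms have equal size and equal true event rates, and let s_Y and s_C be the probabilities that an event is noted. The expected share of recorded events in the yoga arm is

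s_Y / (s_Y + s_C) = r / (r + 1), with r = s_Y / s_C.

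The article gives neither probability, so r is an assumption. With r = 1 the share is 1/2. If capture were strictly proportional to contacts, r = 37 and the share would be 37/38 = 97%. That is an extreme, not an estimate: it ignores the recording of harms outside contacts and the fact that one visit can pick up earlier events. The direction is clear; the size is not.

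**4. What equal collection could show.** With 25 participants at 1:1, the arms hold 12 and 13.

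- No events in n people leaves a one-sided 95% upper bound of 1 − 0.05^(1/n): 22% for n = 12 and 21% for n = 13.
- Power of Fisher's exact test at two-sided 0.05, 13 against 12, summing the binomial probabilities of all tables with p ≤ 0.05: 13% for true rates of 30% against 10%, and 29% for 40% against 10%. These rates are assumptions.

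A comparison of harms here is descriptive even when collection is equal.

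**The case against.** Much can be said for the plan. Harms and adverse events are to be recorded and reported with no restriction to an arm, and controls are monitored at assessments. No between-arm comparison of harms is among the objectives. In a pilot of this size, whether those who attend classes tolerate them is a reasonable safety question, and satisfaction with yoga can only be asked of those who did yoga. The questionnaire is in an appendix that is not shown, and an article commonly leaves the detail of adverse event elicitation to the full protocol. All of this stands. It limits the point, but does not remove it: the restriction of the solicited safety report to one arm is written into Table 2, so it is a stated choice and not an omitted detail.

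A reader might go further in three ways that the article does not support.

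- *That harms cannot be compared.* They can be tabulated by arm; the comparison would be unequal, not impossible.
- *That participant burden is asked of the yoga group only.* Burden is not in the yoga-only row. The coordinator records it, with no arm named.
- *That the feasibility of the control arm is never measured.* Numbers randomised, treated as intended and assessed, attrition, reasons for drop-out and data completeness are all recorded without restriction to an arm. Only the control participants' own view is missing.

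Nor does the article show that controls are especially likely to drop out. It links its concern about attrition to exercise studies with multiple visits, and it offers controls yoga afterwards.

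**Conclusion.** The point holds in a limited form. Solicited self-report on safety, comfort and fatigue, and observation at sessions, exist in the yoga arm only: up to 37 monitored contacts after randomisation (about 26 at 70% attendance) against 1. Any listing of events by arm would therefore reflect ascertainment as well as yoga, most likely to the disadvantage of yoga. The contact count describes unequal opportunity to notice events; it does not estimate the bias.

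For the feasibility aim, the gap is the absence of the control participants' own account of time commitment and of their allocation.

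The conclusion takes Table 2 at its word and assumes that the full protocol has no separate active questioning of controls about events. If it has, the harms part falls away. This is a cheap improvement worth making, not a flaw that undermines the trial.

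**What to change.** - Add to Table 2 a short common form for both arms at the existing 12-week visit: falls, injuries, new pain, health visits and fatigue since baseline, plus time commitment and acceptability of allocation.
- Have the coordinator hand it out, not the blinded assessor, because the answers could reveal the group.
- Keep the satisfaction and benefit items that concern yoga in the yoga-only survey.
- Report events by arm from the common form, descriptively. List events noted in class separately.

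The cost is about one extra page for some 12 control participants at a visit they already attend, a smaller addition for the yoga arm, and a protocol amendment for ethics board review. The form relies on recall over 12 weeks and misses those who leave before the visit; the coordinator already documents reasons for drop-out. Where 12-week visits have already taken place, the report should say that harms were ascertained unequally, and the common form can be carried into the full-scale trial.

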### Outcome Variables and Measurement Tools

#### Demographic Information

We will administer a 13-item paper-based self-reported questionnaire asking about age, sex, gender, ethnicity, education level, employment, income, comorbidities, year diagnosed with HIV, viral load (if known), CD4 count (if known), medications, comorbidities, and physical activity (how often the participant was physically active in the previous week) at baseline to describe the sample and assess group comparability. Participants randomized to the yoga group will be asked to fill out a yoga-readiness questionnaire we created to provide the yoga instructor with safety and injury information.

##### Primary Measures

Many domains of feasibility will be assessed by both participants and study personnel using monitoring processes and a 13-item paper-based post-intervention questionnaire, which includes both questions on a Likert scale ranging from strongly disagree to strongly agree and open-ended questions (see Multimedia Appendix 1):

Project coordination (team building, communication and meetings, collaboration, consensus building, troubleshooting, scheduling, protocol consistency, and timelines). Any issues with (or changes to) the study protocol or scheduling will be documented.Participant issues (recruitment, comfort, satisfaction, safety, attendance, time commitment, attrition, and reasons for ineligibility drop out/declining to participate), as assessed by the postintervention questionnaire and documentation by the study coordinator.Assessment protocol elements (time and personnel requirements, usefulness of outcome variables, participant burden, and feasibility) will be recorded by the study coordinator.Intervention protocols (time, equipment, and personnel requirements) will be recorded by the study coordinator.Data quality (completeness, intra/interparticipant variability, interpretability, and trends) will be checked by the study coordinator. Per the CONSORT checklist, our a priori adherence and satisfaction criteria will be met if participants attend 70% of the yoga sessions and if 70% of the participants are satisfied with the yoga intervention as per the postparticipation questionnaire.

##### Secondary and Tertiary Measures

Cognition, physical performance (balance, walking speed), physical activity, and affective (mental health, quality of life, and medication adherence) evaluations will be administered at baseline and postintervention (12 weeks) by a trained assessor, blinded to the group assignment. The rationale for blinding the assessor is to reduce bias in scoring during the assessment sessions. The estimated length of time for the assessment sessions is 2 hours per participant. We will measure *cognitive function* using the Brief Cognitive Ability Measure (B-CAM), a computerized cognitive test developed for PLWH, using Rasch measurement theory and analysis that takes 30 min to administer [88,89]. The B-CAM provides a measure of global cognition that is calibrated—the intervals between logits are equal, meaning the data are continuous [88,90].

Cognitive domains tested with the B-CAM include visual detection (reaction time), Flanker task (response inhibition) [91], memory (learning and recall of 8 words), Shape 2-back (working memory) [92], Corsi block-tapping forward and back tests (visuospatial memory) [93], verbal fluency (letters F-A-S in English) mini Trail Making Test B (executive function) [94], and the Tower of London test (planning) [95]. The scoring of the B-CAM ranges from 0 to 24, with higher values indicating better global cognition [90]. To reduce the likelihood of practice effects, different versions of the B-CAM are performed at baseline and final assessments [90]. Group-based trajectory analysis has revealed that no practice effects were found at the item level [90].

Self-reported cognition will also be assessed using the C3Q, an 18-item paper-based questionnaire that was developed to estimate the presence and frequency of memory, attention, executive function, visuospatial, speech and language, behavior and emotion, and cognitive challenges among PLWH [82]. The frequency of such challenges are recorded by the participant on a 3-point scale: frequently (almost every day), sometimes (once a week), or rarely (once a month) [82].

*Balance* will be measured using the Community Balance and Mobility (CB&M) test, a high-level balance assessment of tasks performed in the community, developed for people with traumatic brain injury [96]. It is a valid and reliable measure of dynamic postural control in people with traumatic brain injury [96,97] and older community-dwelling individuals [98], and it is not as susceptible to ceiling effects as the Berg Balance Scale [98,99]. *Walking speed* will be measured using the 10-meter walk test because of the association of gait speed with cognitive performance in PLWH [24], its previous use in the HIV literature [26], and its ability to predict survival in older adults [100]. *Depression* will be assessed using the Hospital Anxiety and Depression Scale, a paper-based self-report questionnaire [101], which has very good to excellent internal consistency, test-retest reliability and convergent validity, and acceptable discriminant validity in PLWH [102]. Quality of life will be assessed using MOS-HIV, a paper-based questionnaire that comprises 10 domains (physical function, social function, role function, cognitive function, pain, mental health, energy, health distress, quality of life, and overall health), with good to high internal consistency and construct validity in PLWH [103]. *Physical activity* will be assessed using the Rapid Assessment of Physical Activity, a 9-item paper-based questionnaire that measures moderate and vigorous physical activity, including strength and flexibility within the last week [104]. It was validated in older adults [104], and it has been used in studies with people with HIV [105]. Objective levels of physical activity (total distance walked, and number of steps taken per day) will be measured using accelerometers (Fitbit flex 2) [106]. Accelerometer data will be electronically synced and downloaded after weeks 1 and 12 and stored in an encrypted file. Participants will also be asked about *Medication adherence* (specifically cART), measured with the paper-based Simplified Medication Adherence Questionnaire (SMAQ), which has 72% sensitivity, 91% specificity, and a likelihood ratio of 7.94 for nonadherent patients [107].

### Participant Safety

Participants will be monitored throughout the yoga sessions and the assessments. If a participant presents with any medical or safety concerns, the supervising physiotherapist will provide the appropriate first aid or injury treatment; then, the supervising physiotherapist will refer the participant to the participant’s family physician for follow-up. Any harms or unanticipated effects will be recorded as per the CONSORT checklist [81]. Owing to the low-risk nature of the study, we do not anticipate any additional safety or medical issues associated with the yoga interventions.

## Results

### Data Analysis

All questionnaires and measures will be assessed for missing data. The data will be analyzed to determine if the assumptions for parametric tests are met. Descriptive statistics will be used to characterize the participants. As per the CONSORT extension for pilot studies, means of all outcomes, mean change, and 95% CIs will be calculated for each group separately. We will also follow the Sex and Gender Equity in Research guidelines [108] by disaggregating data by sex and gender. Participant dropouts will also be reported disaggregated by sex.

Independent *t* tests and Fisher exact tests will be used to compare the 2 groups at baseline. If the 2 groups differ at baseline, that variable will be included in the analysis as a covariate. We will analyze quantitative postintervention questionnaire responses using Chi-square tests, and open-ended responses will be analyzed thematically. Intention-to-treat and per-protocol analyses will be used in the analysis of the secondary variables. Changes in outcome variables will be examined between groups and within groups. Floor and ceiling effects will be calculated for the CB&M test. Effect sizes will be reported for each outcome. Alpha level will be set at .05, using 2-tailed for all inferences, and data will be analyzed with SPSS Version 25 (SPSS Inc). As this is a pilot study, sample size calculations are not recommended [81]. This pilot study will not be adequately powered to conclusively state the influence of the intervention on study outcomes, but if trends are promising, a future, more adequately powered trial will be planned. This pilot study will provide preliminary data for future sample size calculations.

Study enrollment began in January 2018, with results expected in October 2019.

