**Results:**

As per the Consolidated Standards of Reporting Trials extension for pilot studies, means of all outcomes, mean change, and 95% CIs will be calculated for each group separately. Two-tailed independent *t* tests and Fisher exact tests will be used to compare groups at baseline. We will analyze quantitative postintervention questionnaire responses using Chi-square tests, and open-ended responses will be analyzed thematically. Intention-to-treat and per-protocol analyses will be used to analyze secondary variables. Changes in outcome variables will be examined between groups and within groups. Effect sizes will be reported for each outcome. A priori adherence and satisfaction criteria will be met if participants attend >70% of the yoga sessions and if >70% of the participants are satisfied with the intervention as determined by a postparticipation questionnaire. Study enrollment began in January 2018, with results expected for October 2019.

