### Participants

We will identify cognitive concerns on the Communicating Cognitive Concerns Questionnaire (C3Q) with a cut-off of 35 points or less [82]; in addition, we will include a maximum total of 25 PLWH who are aged 35 years or older of any gender, are English speaking, live within 50 km of the study site, are able to provide informed consent, and are deemed medically stable as assessed by the Physical Activity Readiness Questionnaire Plus [83]. Study exclusion will include regular participation in a yoga program during the 6 months before study commencement.

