### Randomization

After baseline assessment, an individual not directly involved in the study will randomly assign participants in a 1:1 ratio to the yoga or control group using a random computer generator. Group assignment of each participant will be concealed in individual opaque envelopes that will remain sealed until after completion of the baseline assessment. The number of participants screened and randomized to each group will be recorded, as per the CONSORT extension for randomized pilot trials [81].

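### Covariates are chosen by baseline significance tests and changes are otherwise compared, so each outcome's own baseline value is adjusted for only by chance, at a cost in precision

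*Protocol article*

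**What the plan says.** All statements are in the protocol article.

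- **Baseline tests.** Under Data Analysis, independent t "tests and Fisher exact tests will be used to compare the 2 groups at baseline". The abstract repeats this.
- **Covariate rule.** The next sentence reads: "If the 2 groups differ at baseline, that variable will be included in the analysis as a covariate". No covariate is named in advance, not even the baseline value of the outcome being analysed.
- **Form of the effect analysis.** "Changes in outcome variables will be examined between groups and within groups".
- **Error level.** "Alpha level will be set at .05, using 2-tailed for all inferences".
- **Descriptive summaries.** Following the CONSORT extension for pilot studies, "means of all outcomes, mean change, and 95% CIs will be calculated for each group separately".
- **Size and allocation.** Under Participants, "we will include a maximum total of 25 PLWH". Under Randomization, a person outside the study will "randomly assign participants in a 1:1 ratio to the yoga or control group", after the baseline assessment and with concealed envelopes.
- **Use of the results.** Objectives 2 and 3 are comparisons of yoga with control. The Data Analysis section says the pilot cannot settle the effect of yoga. It also says that promising trends would lead to a larger trial and that the data will feed its sample-size calculation.

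**The concern.** Allocation is random and concealed, so any baseline difference is chance. A significance test between the arms then asks a question whose answer is known, and using it to choose covariates picks them by accident, not by how well they predict the outcome. The model is fixed only once the data are seen.

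The variable that usually predicts a 12-week score best is the same score at baseline. The cognitive, physical and affective scales are all measured at baseline and at 12 weeks, so it is available without further data collection. Under the stated rule it is used only when it happens to cross .05. In all other cases the comparison of changes applies, which in effect fixes the baseline slope at 1 and does not estimate it.

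Within-group change is a smaller, related matter. It does not answer objectives 2 or 3, and set beside a between-group result it can be misread. At stake are the estimates used to judge whether trends are promising and to size the next trial.

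**Working it through.** The article states no power or precision figure for these outcomes, so there is nothing to reproduce.

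**Inputs from the article:** at most 25 participants, 1:1 (taken as 12 v 13); two-sided alpha .05.

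**Assumptions:** correlation r between baseline and 12-week value, shown from 0.3 to 0.9; equal SDs at the two visits, set to 1; normal data; no dropout; differing at baseline means p < .05.

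**1. What the baseline test can detect**

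- Smallest flagged difference: t(.975, 23 df) × √(1/12 + 1/13) = 2.069 × 0.400 = 0.83 SD.
- Power for a true 0.5 SD difference (noncentral t, 23 df): 22%.
- Under randomisation any one variable, including an outcome's own baseline value, is flagged with probability .05. That is the source of the 5%.
- As an illustration, if the 13 demographic items were each tested and independent, the chance of at least one flag would be 1 − 0.95^13 = 49%. Fisher tests are conservative in small samples, so the real figure would be lower.

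**2. Change score against ANCOVA**

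Per-observation variance is 2(1 − r) for the change score and 1 − r² for ANCOVA. The ratio ANCOVA/change is (1 + r)/2. Estimating the slope with N = 25 costs a factor 1 + 1/21.

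| r | (1 + r)/2 | × 22/21 |
|---|---|---|
| 0.3 | 0.65 | 0.68 |
| 0.5 | 0.75 | 0.79 |
| 0.7 | 0.85 | 0.89 |
| 0.8 | 0.90 | 0.94 |
| 0.9 | 0.95 | 1.00 |

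**3. The plan's rule against ANCOVA**

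Simulation: ANCOVA if the outcome's own baseline value is flagged, change score otherwise. The first two columns are the SD of the estimated group difference. The reduction is 1 − (ANCOVA SD / plan SD)².

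| r | Plan's rule | ANCOVA | Variance reduction |
|---|---|---|---|
| 0.3 | 0.454 | 0.391 | 26% |
| 0.5 | 0.390 | 0.355 | 17% |
| 0.7 | 0.306 | 0.293 | 8% |
| 0.8 | 0.252 | 0.246 | 4 to 5% |
| 0.9 | 0.179 | 0.179 | under 1% |

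At r = 0.5, 1/(1 − 0.17) = 1.20, so the loss equals about 20% more participants. At r = 0.7, 1/(1 − 0.08) = 1.09, about 9% more. For an illustrative 0.8 SD effect, power is 48% (plan) v 58% (ANCOVA) at r = 0.5, and 69% v 74% at r = 0.7.

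Type I error under the plan's rule was between 4% and 5% over this range, so it is not inflated.

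**4. Reading within-group tests side by side**

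Suppose both arms truly change by the same amount, in units of the SD of change. The probability that yoga is significant and control is not is p(yoga) × [1 − p(control)], from the one-sample t test.

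- Common change 0.3: p = 0.156 (n = 12) and 0.168 (n = 13). Result 0.156 × 0.832 = 13% if yoga has 12, and 0.168 × 0.844 = 14% if yoga has 13.
- Common change 0.5: p = 0.353 and 0.382. Result 0.353 × 0.618 = 22%, or 0.382 × 0.647 = 25%.
- No change in either arm: 0.025 × 0.975 = 2.4%.

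A between-group test would falsely favour yoga in 2.5% of trials in every case.

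**The case against.** **This is a feasibility pilot.** Feasibility, adherence and satisfaction are the primary measures, cognition and function are secondary or tertiary, and the article disclaims conclusive inference on effect. This stands and lowers the weight. It does not remove the point, because the article gives these estimates a use in planning the next trial.

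**The gain depends on an unknown r.** This stands. At r = 0.9 and N = 25 ANCOVA gains almost nothing. It does not lose in the range examined, so the change carries little risk.

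**An analysis plan may supply the model.** It could, but the article does not leave the matter open: it fixes a rule, and the rule is the problem. The article does not define when groups differ; the tests named just before and the .05 level for all inferences make significance the natural reading.

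A reader might also infer more than the document supports:

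- *That the rule makes the tests invalid.* In the setting checked, where only the outcome's own baseline value is screened, type I error stays at or just below 5%.
- *That the trial will claim yoga worked because yoga improved and control did not.* The article announces no such conclusion, and between-group comparisons are planned as well. The misreading is only a risk, and it needs a common change in both arms. Regression to the mean could produce one on the C3Q, which has a cut-off at screening, but that argument does not carry over directly to the other scales.
- *That using different B-CAM versions at the two visits biases the change.* The article presents the versions as protection against practice effects and reports none at item level. Nothing shows unequal difficulty, and a shift common to both arms would cancel between them.
- *That per-arm means and CIs are a fault.* They follow the cited reporting guidance and are sound as description.

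**Conclusion.** The point holds as one of efficiency and prespecification. The stated rule leaves adjustment for the outcome's own baseline value to a 5% chance event and misses most moderate imbalances. Compared with ANCOVA fixed in advance, it gives up roughly a quarter of the variance at r = 0.3, a sixth at r = 0.5, a twelfth at r = 0.7, and little above 0.8. These sizes rest on the assumed r, equal SDs at the two visits, full follow-up of 12 v 13, and a significance reading of the rule. If imbalance were judged by eye the figures would change, but covariates would still be chosen after seeing the data.

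The grade is should-fix. No confirmatory claim depends on the model, so calling it essential would overstate it. The remedy is nearly free, and with 25 participants the avoidable variance goes straight into the estimates that guide the next trial.

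**What to change.** 1. Delete the conditional-covariate sentence and the baseline tests that drive it, in Data Analysis and in the abstract. Describe baseline characteristics by arm without p values.
2. For each continuous secondary or tertiary outcome, prespecify ANCOVA of the 12-week value on arm plus the baseline value of that outcome. Report the adjusted between-group difference with its 95% CI as the result for objectives 2 and 3.
3. Exempt the Fitbit measures unless their first value is collected before randomisation. Accelerometer data are downloaded after weeks 1 and 12, while allocation follows the baseline assessment, so the first value may come after allocation and would then not be a proper covariate.
4. Keep per-arm means, mean changes and CIs as description, and state that no conclusion about yoga will be drawn from within-group change.

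Cost: a few sentences and one degree of freedom per model (23 to 22 with 25 participants). No new data are needed.
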